Thirdly, a logistic regression model will be considered including both PET and CT, on their original scale, as covariates. This may increase the power and diagnostic accuracy of identifying those who will subsequently be diagnosed with lung cancer. It will provide a risk score and predicted probability of lung cancer for each individual, based on their specific test values. We will then use a cut-off value to decide when a risk score is high (such that we predict an adverse outcome) and when it is low (such that we predict a good outcome). The calibration of the model will be assessed by grouping patients into deciles ordered by predicted risk and considering the agreement between the mean predicted risk and the observed number of true lung cancer cases in each decile (sometimes referred to as the expected versus observed statistic, E/O). The derived diagnostic rule will be cross validated by comparing the classification of each patient with their actual primary outcome of confirmed lung cancer, allowing an estimate of the sensitivity and specificity of the prediction model. Then, by varying the chosen cut-off level, we will produce a receiver operating characteristic (ROC) curve summarising the sensitivity and specificity of the predictive rule across the range of cut-offs. The overall discriminatory ability will be summarised as the Area Under ROC curve (AUC) with 95% confidence interval. The most suitable cut-off level can then also be detected. The internal validity of the final model will also be assessed by the bootstrap re-sampling technique to adjust for over-optimism in the estimation of model performance due to validation in the same dataset that was used to develop the model itself.

If the above methods all show poor accuracy performance (in terms of calibration and/or discrimination), then the logistic regression model will be extended to include additional patient-level covariates (such as time from FDG injection to PET-CT scan), in addition to test results. Demographic information will be considered here as well as clinical and imaging features considered indicative of a higher likelihood of SPN malignancy than unselected patients. The performance of the model will also be evaluated at the

practice-level where possible, to ascertain whether model performance is consistent in each practice or, if not, the variability in performance across practices, and whether it can be improved by tailoring the prevalence used in each practice.

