Predictive values of symptoms for lung cancer diagnosis obtained from previous research [4, 5] and clinical decision support aids based upon these datasets (e.g. RATS [10]), do not distinguish between early and late stage lung cancer. Existing datasets based upon GP paper records do not provide the power to identify symptoms of early stage disease, and risk scores based upon these datasets assume no difference between symptoms of early and late stage LC. Electronic General Practice Research Database (GPRD) datasets, although providing greater power, do not provide detailed information about symptom experiences or record multiple symptoms with accuracy, information which is likely to be necessary to identify symptoms which predict early stage LC. The SPUtNik study provides a unique opportunity to ascertain whether or not it is possible to distinguish between malignant and non-malignant solitary nodules on the basis of symptoms. The collection of symptom data within SPUtNik will allow the identification of symptoms associated with early malignant disease. Apparent associations of symptoms with LC diagnosis in previous research might be explained by confounding; symptoms might be predictive of chronic respiratory disease or lung lesions more generally. The inclusion of symptom data within the SPUtNik Trial would also enable the identification of symptoms which, when incorporated into a diagnostic algorithm might improve the diagnostic performance of FDG-PET and DCE-CT scans. The IPCARD-SPN study will use the IPCARD symptoms risks, and co-morbidities questionnaire within a prospective study design to identify symptoms which distinguish between malignant and non-malignant solitary nodules.

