#### **AIMS:**

- To identify the PPV and NPV of symptoms that distinguish between malignant and non-malignant solitary pulmonary nodules
- To ascertain whether or not the inclusion of symptoms found to distinguish between malignant and non-malignant nodules increases the diagnostic value of DCE-CT and FDG-PET.

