## DATA ANALYSIS

The predictive value of symptoms for lung cancer diagnosis will be identified at 12 (12 months from recruitment/questionnaire completion) and 24 months following questionnaire completion (end of study) for the first IPCARD questionnaire, and at 12 months following questionnaire completion (2 years from recruitment/ at end of study) for the second IPCARD questionnaire.

Logistic regression will be used to obtain unadjusted and adjusted odds ratios for symptoms. The models will be adjusted for age, sex and current smoking status and COPD status. COPD precedes lung cancer diagnosis in 40% to 90% of the cases and differences in prevalence of COPD between early stage and late stage lung cancer might explain differences in symptoms between these groups [14].

COPD will be defined by:

- Abnormal spirometry post-bronchodilator: defined as a forced expiratory volume in 1 second (FEV1) <70% of predicted and forced expiratory volume in 1 second/ forced vital capacity (FEV1: FVC) ratio <0.70. This is based on the American Thoracic Society standards agreed by most respiratory guidelines.

AND/OR

- Clinical diagnosis, by the chest clinic physician, based on the presence of symptoms such as recurrent cough (productive), wheezing, dyspnoea in conjunction with pre-disposing risk factors such as smoking, age and family history.

This data will be drawn from patients' medical records by research staff and will not be taken as part of the study

For the purposes of this study the implications of using a second definition of COPD (based upon evidence of emphysema identified by CT scan) will also be explored. It is possible that early symptoms experienced by those with resectable lung cancer might be explained by emphysema.

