Age, sex and further common comorbidities which are found to differ between the LC and non-LC populations, and share symptoms with lung cancer will be included as covariates in the multivariate models. Previous research has found interactions between symptoms and risk factors to have higher PPVs than symptoms alone [6]. Items to identify individual risk of LC were included in IPCARD to determine the interaction of symptoms and established epidemiological risk factors [13], further refining estimates of individual risk in those with symptoms. Clinically plausible interactions between symptoms and interactions between symptoms and risk factors/comorbidities (pack years smoked, family history of cancer, previous malignancy, previous pneumonia, asthma, and acute respiratory infections) will be tested in the final model.

Multivariable analyses –developing a model to predict lung cancer diagnosis: A multivariable model will be developed which will be adjusted for age, sex, current smoking status, COPD status and common comorbidities where these differ between lung cancer and non-lung cancer. Clinically plausible interactions between symptoms, and interactions between symptoms and risk factors/comorbidities (pack years smoked, family history of cancer, previous malignancy, previous pneumonia, asthma, and acute respiratory infections)

will be tested. All symptoms with an association with LC in univariate analyses will be entered into the final model.

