Modelling strategy: Univariate logistic regression will be used to explore associations between each of the symptoms and the outcome variable (lung cancer). Forward stepwise multiple logistic regression analysis will be used to enter symptom variables into the analysis which were associated with lung cancer in univariate analysis ( $p < 0.05$ ). The criteria for entry into the model will be  $p \leq 0.05$  and criteria for removal will be  $p \geq 0.1$ . To reassess variables discarded through the stepwise process, each in turn will be added to the final model and any improvement in predictive value ( $R^2$ ) noted. The adjusted odds ratios for symptoms will be reported with  $p$  values. Symptoms with an independent relationship with LC will be included in a simple score (each symptom variable is given a value of 1). Analyses will calculate the sensitivity, specificity and predictive values for various levels of cut-offs to determine the optimal threshold at which the score best distinguishes between those with and without lung cancer.

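### The IPCARD-SPN analysis as written gives no estimate for its second aim, because no symptom model contains the PET or DCE-CT result

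*Protocol*

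**What the plan says.** Appendix 6 of the protocol sets two aims. The first is the positive and negative predictive value of symptoms that separate malignant from non-malignant nodules. The second is "To ascertain whether or not the inclusion of symptoms found to distinguish between malignant and non-malignant nodules increases the diagnostic value of DCE-CT" and FDG-PET. The Background of the appendix gives the same purpose: symptoms that "when incorporated into a diagnostic algorithm might improve the diagnostic performance of" the two scans.

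The Data Analysis section then writes out the models:

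- Odds-ratio models: "The models will be adjusted for age, sex and current smoking status and COPD status".
- Prediction model: "A multivariable model will be developed which will be adjusted for age, sex, current smoking status, COPD status and common comorbidities" where these differ between the groups, with interactions among symptoms and between symptoms and risk factors or comorbidities.
- Selection: "Forward stepwise multiple logistic regression analysis will be used to enter symptom variables into the analysis", limited to those with univariate p < 0.05 (entry p ≤ 0.05, removal p ≥ 0.1).
- Product: "Symptoms with an independent relationship with LC will be included in a simple score (each symptom variable is given a value of 1"), with sensitivity, specificity and predictive values reported across cut-offs of that score.

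In the main trial, section 9.1, Statistical analysis (i), states that "a logistic regression model will be considered including both PET and CT, on their original scale, as covariates". That model is extended to patient-level covariates only under a condition: "If the above methods all show poor accuracy performance (in terms of calibration and/or discrimination").

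**The concern.** A question about added value needs the scan results in the analysis, with symptoms judged against them. The sub-study models contain demographics, smoking, COPD, comorbidity and symptoms, but no SUVmax, PET grade or DCE-CT enhancement. CT appears only as a route to an alternative, emphysema-based definition of COPD. No comparison of scans alone with scans plus symptoms is described.

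Followed as written, the second aim gets no estimate. An independent relationship with lung cancer in this strategy means independent of the listed covariates and of the other symptoms. A reader who has the second aim in mind could take a score built from such symptoms as useful on top of imaging, which the analysis would not have tested.

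**Working it through.** **1. Aims against models.** This step needs no arithmetic and carries the point.

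| Analysis | Scans in the model | Symptoms in the model | Serves |
|---|---|---|---|
| Appendix 6, odds-ratio models | no | yes | aim 1 |
| Appendix 6, multivariable and stepwise model | no | yes | aim 1 |
| Appendix 6, symptom score | no | yes | aim 1 |
| Section 9.1, logistic model | yes | no | main trial |
| Section 9.1, extension | yes | not named | only if all earlier methods perform poorly |

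No row holds both scans and symptoms unconditionally, as aim 2 requires.

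**2. The stated power.** Inputs from Appendix 6, Sample Size: 257 with and 118 without lung cancer, two-sided 5%. For 16% vs 30% with the pooled formula:

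- mean proportion = (118×0.16 + 257×0.30)/375 = 0.256
- SE under the null = √[0.256×0.744×(1/118 + 1/257)] = 0.0485
- SE under the alternative = √[0.16×0.84/118 + 0.30×0.70/257] = 0.0442
- power = Φ[(0.14 − 1.96×0.0485)/0.0442] = Φ(1.02) ≈ 84.5%

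The four planning cases in order (5 vs 15%, 16 vs 30%, 22 vs 36%, 34 vs 50%) give 83.8, 84.5, 78.7 and 83.2%, and 78.2, 80.9, 74.9 and 80.1% with a continuity correction. The stated 80% is broadly reproduced. It is the power of an unadjusted comparison of symptom frequency.

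**3. What changes when the scans enter.** Further inputs from section 9.1: PET 92%/90% and DCE-CT 87%/83% sensitivity/specificity. Assumptions: tests dichotomised and independent given disease, adjusters left out. Each case used 2,000 simulated data sets of 375 and a likelihood-ratio test at 5%.

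| Type of symptom | Retained, scans left out | Retained, scans in model |
|---|---|---|
| Informative beyond the scans, at the four planning differences | 80-89% | 31-34% |
| Depends only on the PET result, set to give the same four differences | 80-87% | 4-5% |

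For the second row at 16% vs 30%, solving 0.92a + 0.08b = 0.30 and 0.10a + 0.90b = 0.16 gives symptom frequencies of a = 0.314 if PET is positive and b = 0.143 if negative. If about 70% of questionnaires return (180 and 83 patients, an assumption), the with-scan figures become 23-24% and 5-6%.

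**4. Illustrative AUC.** Cells are PET+/DCE+, PET+/DCE−, PET−/DCE+, PET−/DCE−. Under independence:

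- malignant: 0.8004, 0.1196, 0.0696, 0.0104
- benign: 0.017, 0.083, 0.153, 0.747

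The AUC sums, over cells, the malignant proportion times (benign proportion in lower-ranked cells + half the tied proportion):

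0.8004×0.9915 + 0.1196×0.9415 + 0.0696×0.8235 + 0.0104×0.3735 = 0.967.

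Splitting every cell by a symptom at 30% vs 16% (odds ratio (0.30/0.70)/(0.16/0.84) = 2.25) and repeating the sum gives 0.970, a gain of about 0.003.

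Independence conflicts with section 9.1, which reports both tests positive in 114/130 = 0.877 of malignant cases; independence implies 0.92×0.87 = 0.80. With joint positivity at its cap of 0.87, the malignant cells become 0.87, 0.05, 0, 0.08:

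- Dependence in malignant cases only: 0.87×0.9915 + 0.05×0.9415 + 0.08×0.5265 = 0.952, rising to 0.957 with the symptom (gain about 0.006 before rounding).
- Maximal dependence in benign cases too (cells 0.10, 0, 0.07, 0.83; an assumption): 0.87×0.95 + 0.05×1 + 0.08×0.485 = 0.915, rising to 0.926 (gain about 0.011).

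**The case against.** The best defence is that the analysis is unwritten rather than wrong. The covariate list belongs to a model for predicting lung cancer from symptoms, which is right for aim 1, and nothing forbids a further model. A statistical analysis plan that is not shown could supply it. This stands in part: leaving the scans out is no fault for aim 1. But the appendix did not leave its modelling open. It fixes covariates, interactions, stepwise thresholds and the final score, and ends without the comparison that aim 2 requires.

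Section 9.1 also offers some shelter. Its extension admits clinical features alongside the scans, and symptoms might be read as such. It does not name them, however, and it runs only if every earlier method performs poorly, whereas aim 2 is unconditional.

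Three stronger readings are tempting and are not supported:

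- *That aim 2 cannot be answered.* Questionnaires carry the trial code and diagnosis comes from trial data, so the data suffice once the analysis is stated.
- *That symptoms mirroring the scans will be reported as false findings.* The protocol gives no evidence that such symptoms exist. If a symptom occurred in 30% of PET-positive and 16% of PET-negative patients, its frequency would be 0.92×0.30 + 0.08×0.16 = 28.9% in cancer and 0.10×0.30 + 0.90×0.16 = 17.4% otherwise. Retaining it, in about 68-69% of simulated trials, is power for a real association and not an error rate.
- *That symptoms add almost nothing.* The gain of 0.003 rests on independence, which the protocol's own joint figure contradicts.

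IPCARD-SPN is also optional and absent from the trial objectives, so no main-trial estimate is affected.

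**Conclusion.** The point holds for aim 2 only. The written-out models answer aim 1 and give no estimate of what symptoms add to DCE-CT and PET. That follows from the text alone and needs no simulation.

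The numbers show why aim 1 results cannot stand in for aim 2. A symptom of the planned size is retained about equally often whether or not it adds anything to the scans (80-89% against 80-87%). With the scans in the model the two separate, at 31-34% against 4-5%. Power for added value is therefore well below the stated 80%. The 31-34% assumes dichotomised tests that are independent given disease, and no adjusters. The AUC gain is best given as a range of about 0.003 to 0.011, since it depends on how strongly the two tests agree within disease groups.

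This should be corrected, as a stated sub-study aim otherwise goes unanswered. It does not touch the main trial's primary results.

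**What to change.** Keep the present Appendix 6 models for aim 1, and describe retained symptoms as independent of demographics, comorbidity and other symptoms only. Add an aim 2 analysis:

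1. Base logistic model: PET (SUVmax) and DCE-CT (enhancement) on their original scale, plus the adjusters already listed.
2. Add only the symptom score, or the retained symptoms. The adjusters must already be in the base model; otherwise any gain from age or smoking would be credited to symptoms.
3. Report the likelihood-ratio test and the change in AUC, with a bootstrap optimism-corrected interval that repeats the symptom selection in each resample.
4. State in Sample Size that the 80% power applies to unadjusted symptom comparisons (aim 1), and give the lower power for added value with its assumptions.

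The cost is some wording and one extra model on data already collected. The downside is that the reported increment will probably be small or imprecise.

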#### **SAMPLE SIZE**

Sample size calculations for the analyses (assuming a two sided 5% alpha) using 257 cases of lung cancer and 118 without LC, gave 80% power to detect a difference in a rare or low frequency variable of 10% (from 5% in non-LC to 15% in LC) or 80% power to detect a difference in a more common variable of 14% (from 16% in non-LC to 30% in LC or from 22% in non-LC to 36% in LC). For a more prevalent LC symptom, 257 cases of lung cancer and 118 without LC gave 80% power to detect a difference of 16% (from 34% in non-LC to 50% in LC). The SPUtNik Trial, which anticipates identifying 257 cases of LC and 118 non-malignant lesions, is adequately powered to detect odds ratios for all symptoms (except rare symptoms) likely to have diagnostic value (>2 or <0.5) in clinical populations.

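### IPCARD-SPN sub-study: two model-building rules that cannot both be followed, and a symptom score evaluated on the patients used to build it with no optimism correction stated

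*Protocol*

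**What the plan says.** Two adjacent paragraphs of Appendix 6 (Data Analysis) describe how the symptom model is built.

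- **Multivariable analyses.** After listing the adjustment covariates and interactions, it ends: "All symptoms with an association with LC in univariate analyses will be entered into the final model". This sentence gives no p threshold and no further selection step.
- **Modelling strategy.** Here the plan reads: "Forward stepwise multiple logistic regression analysis will be used to enter symptom variables into the analysis which were associated with lung cancer in univariate analysis". The threshold for that first screen is p < 0.05; entry is at p ≤ 0.05 and removal at p ≥ 0.1. On dropped symptoms it continues: "To reassess variables discarded through the stepwise process, each in turn will be added to the final model and any improvement in predictive value", taken as the change in R², is recorded. No rule says whether a re-added variable is kept.

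The modelling paragraph then turns to the score: "Symptoms with an independent relationship with LC will be included in a simple score", with one point per symptom. Sensitivity, specificity and predictive values are calculated at several cut-offs, and the best cut-off is chosen from them. No threshold defines an independent relationship.

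The appendix bases its power statement on 257 patients with lung cancer and 118 without. Taking part in IPCARD-SPN is an optional element of the SPUtNik consent.

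For the main logistic model, Section 9.1, Statistical analysis (i), requires bootstrap resampling to correct performance for optimism. Part (ii) plans bootstrapping and shrinkage where appropriate. Appendix 6 contains no equivalent.

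**The concern.** There are two separate problems.

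**Conflict.** The term final model has two meanings. In one paragraph it holds every symptom that is associated on its own. In the next it is what remains after stepwise selection. No sentence says which governs. The adjusted odds ratios, their p values and the symptoms that earn a point all come from that model, so the published symptom list could rest on a choice made at analysis.

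**Optimism.** Screening, selection, scoring, choice of cut-off and evaluation all use the same patients. The smaller outcome group is about 118 at the planned prevalence if everyone takes part, and fewer if some decline. The questionnaire offers many candidate symptoms. Performance measured this way is too favourable under either rule. A reader comparing it with the optimism-corrected performance of the imaging model would not be comparing like with like.

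**Working it through.** **1. The passages side by side.** The plan gives no figure for this point, so there is nothing to reproduce. Let U be the set of symptoms associated with lung cancer one at a time, and S the subset of U that survives stepwise selection.

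- Multivariable analyses paragraph: final model = U.
- Modelling strategy paragraph: final model = S. Discarded variables are added to it in turn, so they are outside it.

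The two agree only if S = U, that is, if stepwise discards nothing. The score takes the symptoms with an independent relationship. Under the first rule that means symptoms still associated in the model holding all of U (criterion unstated). Under the second it is naturally S.

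**2. How often do the rules diverge?** This was a simulation with 60 replicates per setting.

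- From Appendix 6: 257 with and 118 without lung cancer; symptom frequency 22% against 36% for a truly associated symptom; univariate p < 0.05; entry p ≤ 0.05; removal p ≥ 0.1.
- Assumed, not in the documents: 20 or 40 binary symptoms in blocks of 5; latent within-block correlation 0.2, 0.4 or 0.6; 30% of symptoms truly associated; no covariates; under the first rule, independent means p < 0.05 in the full model.

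| Symptoms | Correlation | Mean in model, all entered | Mean in model, stepwise | Mean in score, all entered then p < 0.05 | Models differ | Scores differ |
|---|---|---|---|---|---|---|
| 20 | 0.2 | 5.5 | 4.6 | 4.5 | 65% | 8% |
| 20 | 0.4 | 5.4 | 4.2 | 4.1 | 78% | 22% |
| 20 | 0.6 | 5.5 | 4.0 | 3.6 | 80% | 28% |
| 40 | 0.2 | 10.8 | 8.6 | 8.3 | 92% | 33% |
| 40 | 0.4 | 10.3 | 7.7 | 7.2 | 97% | 55% |
| 40 | 0.6 | 10.9 | 7.4 | 6.8 | 100% | 72% |

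Under stepwise, the score is the set of retained symptoms, so its mean size equals the stepwise model's. With 60 replicates the Monte Carlo standard error is at most √(0.5 × 0.5 / 60) = 0.065, so the percentages are approximate.

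Further runs used 75 symptoms, close to a count of roughly 70 to 80 symptom items in the questionnaire. Frequencies were 10% to 40%, and 8 symptoms had a true odds ratio of 2. Models differed in 83% to 93% of runs and scores in 42% to 47%. In the runs that recorded it, mean score size was 6.4 to 6.9 against 6.8 to 7.1 symptoms, with average overlap (Jaccard) about 0.91.

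**3. How large is the optimism?** With 75 candidates and no true effect, a screen at p < 0.05 passes on average 75 × 0.05 = 3.75 symptoms by chance. The smaller outcome group supplies 118 / 75 ≈ 1.6 patients per candidate.

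| Setting (75 symptoms, 257/118) | AUC in trial data | AUC in new data |
|---|---|---|
| 8 true symptoms, odds ratio 2 | 0.70 to 0.71 | 0.61 to 0.63 |
| No true symptom | 0.59 to 0.62 | 0.50 |

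The ranges span two simulation runs and both rules. With round values, optimism is 0.70 − 0.62 = 0.08 with true symptoms and 0.60 − 0.50 = 0.10 with none. In the first case 0.08 / (0.70 − 0.50) = 40% of the apparent discrimination above chance is not real. AUC stands in here for sensitivity, specificity, PPV and NPV at the chosen cut-off, which were not simulated separately.

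**The case against.** **Entered may mean offered as a candidate.** On that reading the two paragraphs describe one procedure. It is probably what was intended, but the wording does not support it: the sentence says the symptoms go into the final model, and the next paragraph uses that term for the model left after discarding.

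**The effect on the score is limited.** This stands. A reader might infer that the two rules yield quite different scores, because the models differ in nearly every run with 40 symptoms. That compares models, not scores. Only symptoms with an independent relationship earn a point under either rule, so the scores can coincide, and when they differ they overlap heavily.

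**Little is gained by choosing a rule late.** This also stands for performance, since AUC is nearly the same under both. A reader might infer that one paragraph could be picked to make the score look better, and the simulations do not support that. What changes is which symptoms and adjusted odds ratios are reported.

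**Validation may be left to an analysis plan.** Partly fair. Appendix 6 does not rule out a correction, and a plan not shown here may add one. But the appendix specifies the procedure through to the reported predictive values and the choice of cut-off, and followed as written it overstates performance. The same protocol does state the correction for its main logistic model.

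**It is an optional sub-study.** True. The primary accuracy and economic outcomes are untouched. So are the unadjusted odds ratios and the PPV and NPV of single symptoms, which do not depend on the selection rule.

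**Conclusion.** The point holds, with two parts of different kinds.

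The contradiction follows from the text alone: the two paragraphs cannot both be followed once stepwise selection drops a symptom. They usually give different final models (65% to 100% of simulated runs with 20 or 40 symptoms) and can give different scores (8% to 72%). Divergence is more frequent with more, and more strongly correlated, symptoms. Discrimination is similar under both.

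The optimism arises under either rule. Illustratively, AUC is about 0.70 apparent against 0.62 in new data, and about 0.60 against 0.50 when nothing is predictive. All these sizes rest on assumed symptom numbers, frequencies and correlations, on binary coding and on models without covariates. The direction of the bias does not rest on those particular values.

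The documents do not support a claim that the scores must differ, or that the main diagnostic accuracy analysis is affected. The correction should be made before the sub-study is analysed.

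**What to change.** Three wording changes in Appendix 6, Data Analysis:

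1. Amend the last sentence of the multivariable analyses paragraph so that symptoms associated at p < 0.05 one at a time are candidates for the single procedure in the modelling strategy paragraph, whose result is the final model. Say whether a re-added variable can be kept, and on what criterion.
2. State the criterion for an independent relationship, for example retention in that final model.
3. Report sensitivity, specificity, PPV, NPV and AUC of the score corrected for optimism, by repeating the univariate screen, the selection, the scoring and the cut-off choice in each bootstrap sample. This is in line with what Section 9.1 requires for the main logistic model.

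A penalised model is an option, not a requirement. It would change the planned one-point-per-symptom score and would not directly supply the adjusted odds ratios with p values that the appendix promises.

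The cost is some extra analysis work and less favourable reported performance. No new data are needed and patients are not affected.

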The questionnaire has been validated with a CXR population (NIHR funded IPCARD Feasibility Study: co-lead by [name] and [name]). This has enabled the addition of descriptors of symptoms of non-malignant chest and respiratory disease which might have discriminatory value for LC. Participants with early stage LC, late stage LC, COPD, asthma and heart disease have been purposively sampled within qualitative research to ensure that IPCARD adequately records the symptom experiences of these groups. Cognitive and semi-structured interviews have been used to establish the content validity of the questionnaire and the high quality of the symptom data obtained. Test-retest reliability will be evaluated by September 2012. In CXR populations refusal rates have been low (approximately 5%) and data completion high (>80%). Most non-response is accounted for by participants taking partially completed questionnaires away from the clinical site and not returning them by post. The average response rate for the two centres that have now completed their second episode of recruitment is >70%.

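### The IPCARD-SPN simple score gives every retained symptom one point with no sign, so a symptom that is rarer in lung cancer would count towards it

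*Protocol*

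**What the plan says.** All of this is in Protocol Appendix 6, the IPCARD-SPN sub-study.

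- **Selection (Data Analysis, modelling strategy).** The symptoms put forward for the stepwise logistic model are those "which were associated with lung cancer in univariate analysis" at p<0.05. Entry is at p≤0.05 and removal at p≥0.1. No condition is placed on the direction of the association.
- **Score (same paragraph).** "Symptoms with an independent relationship with LC will be included in a simple score (each symptom variable is given a value of 1").
- **Use (same paragraph).** Sensitivity, specificity and predictive values are calculated at various cut-offs, "to determine the optimal threshold at which the score best distinguishes between those with and without lung cancer".
- **Expected effects (Sample Size).** The calculation is made "assuming a two sided 5% alpha", and the sub-study is called "adequately powered to detect odds ratios for all symptoms (except rare symptoms) likely to have diagnostic value (>2 or <0.5) in clinical populations".
- **Questionnaire content (IPCARD Development).** After work in a chest X-ray population: "This has enabled the addition of descriptors of symptoms of non-malignant chest and respiratory disease which might have discriminatory value for LC".

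**The concern.** Selection by p-value lets in associations of either direction. The score then gives each selected symptom the same value, 1, and mentions no sign. A symptom that is less common in lung cancer than in benign nodules would, once retained, move a patient towards a cancer classification.

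The protocol itself foresees such symptoms. It counts odds ratios below 0.5 as diagnostic, and it added descriptors of non-malignant disease because they might discriminate. Section 5.3 also notes that some eligible nodules have an infective or inflammatory component, and the questionnaire asks about phlegm, wheeze and current chest infection. It is plausible, though not established, that some of these are commoner in the benign group.

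At stake are the discrimination of the simple score, its chosen cut-off, and the sensitivity, specificity and predictive values reported at that cut-off.

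**Working it through.** **Inputs from the protocol (Appendix 6, Sample Size).** 257 lung cancers and 118 without; two-sided 5% alpha; 80% power for 5% v 15%, 16% v 30%, 22% v 36% and 34% v 50% (non-cancer v cancer).

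**1. The protocol's own power figures.** The formula is power = Φ{[|d| − c − 1.96·√(p̄(1−p̄)(1/118+1/257))] / √(p0(1−p0)/118 + p1(1−p1)/257)}. Here d = p1 − p0, p̄ is the pooled proportion, and c is 0, or ½(1/118+1/257) with continuity correction.

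| Non-cancer v cancer | Odds ratio | Power, uncorrected | Power, corrected |
|---|---|---|---|
| 5% v 15% | 3.35 | 0.838 | 0.782 |
| 16% v 30% | 2.25 | 0.845 | 0.809 |
| 22% v 36% | 1.99 | 0.787 | 0.749 |
| 34% v 50% | 1.94 | 0.832 | 0.801 |

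Each row agrees with 80% to within 2 points under one of the two forms. No single form fits all four, but the point does not depend on that.

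**2. Would an inverse symptom be selected?** Reverse the third row: 36% in non-cancer and 22% in cancer, odds ratio (0.22/0.78)/(0.36/0.64) = 0.50. Uncorrected power is 0.805, against 0.787 for its positive counterpart. The univariate screen would pick up either about equally often.

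**3. Effect on the score.** Assumed: six independent yes/no symptoms, five at 22% v 36% and one at 36% v 22%. Scoring the inverse symptom −1, or giving 1 for its absence, shifts every score by the same constant, so the two codings rank patients identically.

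A normal approximation, AUC ≈ Φ(difference in means / √sum of the two variances), can be checked by hand:

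- Each symptom contributes 0.36×0.64 = 0.2304 in one group and 0.22×0.78 = 0.1716 in the other. The variance sum is 6×(0.2304+0.1716) = 2.412, root 1.553, whichever sign is used.
- +1 for all: mean difference 5×0.14 − 0.14 = 0.56; Φ(0.56/1.553) = Φ(0.361) = 0.64.
- Signed: mean difference 6×0.14 = 0.84; Φ(0.84/1.553) = Φ(0.541) = 0.71.
- Inverse symptom left out: mean difference 0.70, variance sum 5×0.402 = 2.01; Φ(0.70/1.418) = Φ(0.494) = 0.69.

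The exact AUC, P(S1>S0) + ½P(S1=S0) from the full distributions of the sums, is 0.636, 0.699 and 0.682 respectively. An inverse symptom at +1 is therefore worse than no symptom at all.

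The best cut-off also changes. With +1 for all, sensitivity is 0.66 and specificity 0.55 (Youden index 0.21). Signed, they are 0.52 and 0.78 (0.29).

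**4. Range with one inverse symptom (exact AUC, +1 for all v signed).**

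| Assumed rates | 1 of 5 | 1 of 6 | 1 of 7 |
|---|---|---|---|
| 22%/36% and mirror | 0.612 v 0.682 | 0.636 v 0.699 | 0.657 v 0.715 |
| 30% in non-cancer, OR 2.5 or 0.4 | 0.682 v 0.747 | 0.712 v 0.770 | 0.738 v 0.789 |
| 30% in non-cancer, OR 2.0 or 0.5 | 0.635 v 0.692 | 0.659 v 0.711 | 0.681 v 0.727 |

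The loss is about 0.05 to 0.07 throughout. With no inverse symptom the two scores are the same (0.699 for six symptoms at 22%/36%).

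**The case against.** **The sign is not stated, rather than stated wrongly.** A value of 1 can be read as a unit weight replacing the model coefficient, with coding left to the analyst or to a statistical analysis plan. It is true that the text nowhere says that direction is ignored; that is a literal reading of a sentence silent on sign. But the protocol does fix the weight, and the three natural repairs (subtract, reverse-code, leave out) do not all give the same score. Choosing among them after the directions are known adds an undeclared decision to a cut-off that is already data-driven.

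**Inverse symptoms may be few or absent.** All four worked differences in the Sample Size section are higher in lung cancer. The models adjust for COPD and for comorbidities that differ between groups, which should remove some inverse signals. Asthma is an illness item listed among the risk factors and comorbidities, not a symptom descriptor. This stands, and it limits the plausible size: nothing in the documents suggests that a third or a half of the retained symptoms would be inverse.

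**Stronger readings that the documents do not support.**

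- A reader might infer that the score would rank patients in the wrong order. No AUC calculated here falls below 0.5; the effect is lost discrimination, not reversal.
- A reader might infer that the sub-study could conclude that symptoms do not separate malignant from benign nodules. The unadjusted and adjusted odds ratios are obtained whatever happens to the score, and they keep each direction visible.
- A reader might take the Background remark that "symptoms might be predictive of chronic respiratory disease or lung lesions more generally" as a forecast of inverse associations. In context it concerns confounding of earlier findings, which points to weaker associations and not to odds ratios below 1.

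**Conclusion.** The point holds as a gap in the score rule. Followed literally, Appendix 6 scores a retained symptom with an adjusted odds ratio below 1 towards lung cancer, and nothing else in the appendix prevents it. The protocol's own threshold of below 0.5 shows that such symptoms are contemplated.

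The size is conditional. It rests on independent symptoms, assumed rates, five to seven retained symptoms and exactly one of them inverse, so the AUC loss is an illustration and not a forecast. The scope is also narrow: one derived score in an optional questionnaire sub-study. The primary accuracy endpoints and the reported odds ratios do not depend on it.

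**What to change.** In Appendix 6, Data Analysis, modelling strategy, add to the score sentence that a symptom with adjusted odds ratio above 1 scores +1 and one with adjusted odds ratio below 1 scores −1 (equivalently, its absence scores 1). Limiting the score to symptoms with adjusted odds ratio above 1 would also remove the fault, but it discards information (0.682 against 0.699 in the six-symptom example). Whichever is chosen should be written down before the symptom associations are examined.

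The cost is one sentence. No data or patients are added, the score stays unit-weighted, and if no inverse symptom is retained the result is unchanged.
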